##### Therapy (T1 to T5)

We will assess study outcomes before the start of therapy, after the 8th, 15th and 20th hour of therapy, as well as after therapy has ended. At each time of assessment, patients will participate in an online survey (UNIPARK) including study outcomes (Table 1). The assessment will be conducted at the IMP. Baseline data (T1) will be scheduled no more than 5 days before the first therapy session. Therapy process (T2 to T4) will be assessed no more than 5 days after the 8th, 15th and 20th hour of therapy. The primary endpoint (T5) will be defined by a joint patient-therapist decision to end therapy or by the end of 26 hours of therapy. All outcome variables will be assessed anew, along with in- and outpatient health care service data. A post-SCID and social network interview will also be conducted. Like the pre-SCID, the post-SCID interviews will be rated by independent raters considering primary and secondary diagnoses.

**Table 1 Tab1:** Assessment measures and application plan

Purpose	Perspective	Domain	Instrument	Screening	Baseline	8th, 15th, 20th hour of therapy	End of therapy, no later than 26th hour of therapy	9 and 12 months after beginning of therapy
					T1	T2 to T4	T5	T6 and T7
Screening	Pat	Social anxiety	LSAS-SR	X				
	Diag	Mental disorder SAD	SCID: SAD	X				
Outcome	Diag	Mental disorders	SCID I, II	X			X	
	Pat	Social anxiety	LSAS-SR	X	X	X	X	X
	Pat	Social anxiety	SIAS	X	X	X	X	X
	Pat	Social anxiety	SPS	X	X	X	X	X
	Diag	Global functioning	GAF	X	X		X	
	Pat	Depression	BDI-II	X	X	X	X	X
	Pat, Ref	General symptom severity	BSI	X	X	X	X	X
	Pat, Ref	Experience of social systems	EXIS	X	X	X	X	X
	Pat, Ref	Evaluation of social systems	EVOS	X	X	X	X	X
	Pat, Ref	Dyadic adjustment	DAS-12	X	X	X	X	X
	Pat	Interpersonal problems	IIP-32	X	X	X	X	X
	Pat, Ref	Symptom adjustment	ASS	X	X	X	X	X
	Ref	Burden	BAS		X	X	X	X
Process	Pat, T	Therapeutic alliance	SACiP			X	X	X
	Pat, T	Therapeutic relationship	SRS			X	X	X
	Pat	Therapy motivation	URICA			X	X	X
	Pat, T	Credibility	OAT		X			
Therapists	T	Common therapist factors	DPCCQ		X	X	X	X
Quality	R	Adherence and competence	STAS, CTAS-SP		X	X	X	X
Additional service	Pat	Service receipt	CSSRI-EU				X	X

Diag, diagnostician; Pat, patient; R, researcher; Ref, reference person (most important significant other); T, therapist. ASS, Adjustment to Symptomatology Scale; BAS, Burden Assessment Scale; BDI-II, Beck Depression Inventory II; BSI, Brief Symptom Inventory; CSSRI-EU, Client Sociodemographic and Service Receipt Inventory; CTAS-SP, Cognitive Therapy Adherence Scale for Social Phobia; DAS-12, Dyadic Adjustment Scale; DPCCQ, Development of Psychotherapist Common Core Questionnaire; EVOS, Evaluation of Social Systems; EXIS, Experience in Social Systems; GAF, Global Assessment of Functioning; IIP-32, Inventory of Interpersonal Problems, short form; LSAS-SR, Liebowitz Social Anxiety Scale, self-report measure; OAT, Opinion About Treatment; SACiP, Scale for the Multiperspective Assessment of General Change Mechanisms in Psychotherapy; SCID I,II, Structured Clinical Interview for DSM Disorders I and II; SCID: SAD, Structured Clinical Interview for DSM disorders: Social Anxiety Disorders; SIAS, Social Interaction Anxiety Scale; SPS, Social Phobia Scale; SRS, Session Rating Scale; STAS, Systemic Therapy Adherence Scale; URICA, University of Rhode Island Change Assessment Scale

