### Ethical consideration

CBT will be practiced at the Center for Psychological Psychotherapy (CPP), Heidelberg University, and ST at the Institute of Medical Psychology (IMP), Heidelberg University Hospital. All therapies will be recorded. The pilot study design, the measurement times and instruments are aligned with the studies of Willutzki and colleagues [5], Rakowska and the SOPHO-NET [48]. This research was approved by the Ethics Committee of the Heidelberg Medical Faculty (S-190/2014). Written informed consent will be obtained from each interested person. Staff will send the study information, informed consent and declaration about the usage of DVD records to each interested person after the initial telephone interview. The staff will be available for any questions on the telephone or face-to-face at the IMP during workdays. All interested persons will be informed about their rights to end their participation at any time without negative consequences. Confidentiality will be maintained at all levels of the pilot study by staff members, diagnosticians, therapists, supervisors and researchers. All of them have to declare bindingly that they will give no information to third persons. Additionally, we will work with identification codes for each interested person and patient. All data will be saved pseudonymized on the IMP server. This pilot trial will be conducted in accordance with the Declaration of Helsinki [49], as well as with the State Chamber of Physicians of Baden-Wuerttemberg, Germany.

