##### Follow-up (T6 and T7)

We will assess patients at 9 and 12 months after the beginning of therapy. Again, patients will participate in the online survey including the outcomes (Table 1). The assessment will be conducted at the IMP. The study will close 12 months after the beginning of therapy of the last included patient.

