### Blinding and allegiance

#### Blinding

Patients will be informed about their assignment (no blinding, open trial), the general study aims and procedures, but not about specific hypotheses. Blinding will not be feasible since both the CPP and IMP are well known for their specific therapy orientation, and because of the focus on the external validity and generality of the pilot study to routine care [53]. Outcome assessments at all points in time will be conducted online (UNIPARK), and no blinding of assessors will be needed. Pre- and post-SCID diagnostics will be blinded and the assessors will not know the study arm in which each patient will be treated.

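### The T1–T7 self-reports, including the three primary outcomes, are placed at the IMP, which is the treatment site of the systemic therapy arm only

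*Protocol article*

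**What the plan says.** The Ethical consideration section separates the arms by site: "CBT will be practiced at the Center for Psychological Psychotherapy (CPP), Heidelberg University, and ST at the Institute of Medical Psychology (IMP), Heidelberg University Hospital". The section Therapy (T1 to T5) describes the mode of data collection, "At each time of assessment, patients will participate in an online survey (UNIPARK) including study outcomes (Table 1"), and then gives the place: "The assessment will be conducted at the IMP". The section Follow-up (T6 and T7) repeats it: "The assessment will be conducted at the IMP. The study will close 12 months after the beginning of therapy of the last included patient". No matching arrangement at the CPP and no neutral site is named.

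The Blinding section states that patients know their assignment. It gives as one reason why blinding is not feasible that "both the CPP and IMP are well known for their specific therapy orientation". It then says that, because the outcomes are collected online, "no blinding of assessors will be needed". The Allegiance section accepts that preference for a treatment can bias outcome data and relies on the two-centre set-up to balance it. Biases and limitations lists openness, self-presentation of patients and imperfect control of allegiance, but not the place of assessment.

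**The concern.** The three primary outcomes are patients' own ratings in an open trial, so the conditions under which they are given matter. Here one condition, the setting, is tied to the arm. An ST patient answers at the centre that treats him or her; a CBT patient answers at the centre that hosts the other therapy. The protocol's reasoning on blinding deals with assessors. It does not deal with a setting that carries a known therapy orientation. The two-centre design is the stated safeguard against allegiance, yet measurement takes place at one of the two centres.

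The pilot's main product is an effect size for ST against CBT, to be used to size a confirmatory trial. An arm-linked measurement condition enters that estimate directly, and no analysis of these data can remove it, because within each arm the setting does not vary.

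**Working it through.** The point rests on reading the sections together. The arithmetic at the end only gives a scale.

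**Sections side by side**

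1. Treatment site: CPP for CBT, IMP for ST (Ethical consideration).
2. Assessment site: IMP for both arms at T1–T5, which includes the primary endpoint T5, and at T6–T7 (Therapy; Follow-up).
3. Outcome type: LSAS-SR, SIAS and SPS are completed by the patient (Table 1; Primary outcome measures).
4. Knowledge of arm: patients are told their arm after randomization (Screening and diagnostic process). T1 falls at most 5 days before the first session, so on the natural reading they already know it at T1.
5. From 1 and 2, the assessment site is the treatment site in one arm and not in the other, at all seven time points.

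**What cancels and what does not**

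Write s(ST, t) and s(CBT, t) for the setting effect in each arm at time t.

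- The endpoint comparison planned under Statistical analyses (t-test or Mann–Whitney U test) carries a bias of s(ST, T5) − s(CBT, T5). A shift common to both arms cancels; a shift that differs by arm does not.
- Contrast A in the mixed-design ANOVA (baseline to end of therapy) carries a bias of [s(ST, T5) − s(ST, T1)] − [s(CBT, T5) − s(CBT, T1)]. A shift that is constant over time cancels even if it differs by arm. One that grows does not. Growth is plausible because at T1 no ST patient has yet been treated at the IMP, whereas by T5 each has had up to 26 hours of therapy.

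**Scale, with an assumed shift**

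The protocol's reference figure reproduces first. Per-arm n = 2(1.960 + 0.842)²/d² = 15.70/d². For d = 0.3, 15.70/0.09 = 174.4, so 175 per arm and 350 in total, as stated under Design and sample size. The pilot's 32 is 32/350 = 9.1 % of this.

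The standard error of a standardized difference with 16 per arm is √(2/16) = 0.35 SD.

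The documents give no size for a site effect. Assume a true difference of 0.5 SD in favour of CBT and a net shift of 0.1 to 0.2 SD, at 80 % power and two-sided 5 %:

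| Shift | Observed d | n per arm | Total |
|---|---|---|---|
| none | 0.5 | 15.70/0.25 = 62.8, so 63 | 126 |
| 0.1 towards ST | 0.4 | 15.70/0.16 = 98.1, so 99 | 198 |
| 0.2 towards ST | 0.3 | 175 | 350 |
| 0.1 towards CBT | 0.6 | 15.70/0.36 = 43.6, so 44 | 88 |
| 0.2 towards CBT | 0.7 | 15.70/0.49 = 32.04, so 33 | 66 |

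Shifts of this size are below the pilot's standard error, so they would not show in the data. They would still alter a sample size planned from its estimate.

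**The case against.** The strongest reply is that the sentence may mean only that the IMP runs the survey. It directly follows the description of an online survey, the Blinding section says outcome assessments at all time points are done online, and the data are stored on the IMP server. On that reading no patient need visit the IMP, and the setting argument falls away. This is possible, but it is not the plain wording, and the sentence appears twice. The protocol needs a clarification on either reading.

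A second reply is that a single common site is a reasonable form of standardization, and that baseline and endpoint share it. This stands in part: a constant setting effect drops out of change scores. It does not drop out of the direct endpoint comparison if it differs by arm, and an effect that develops during therapy drops out of neither.

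A third reply is that all analyses are exploratory and that imperfect control of allegiance is disclosed. That is true, and it limits the weight of the point, but the disclosure does not mention where outcomes are collected.

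A reader might infer more than the documents support:

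- **Extra travel and selective drop-out of CBT patients at T6 and T7.** Not shown. By the protocol's schedule regular therapy has ended in both arms by then, booster sessions appear in both manuals, and no distances are given.
- **An unfamiliar site for CBT patients.** Not shown. The IMP is also the study office, where any interested person could meet staff before allocation.
- **ST patients answering in front of their therapists.** Not shown. The ST therapists are trainees of two outside institutes, nobody is said to be present at completion, and the primary scales measure the patient's anxiety rather than the therapy.
- **Every outcome being affected.** Too broad. The screening LSAS-SR goes by post before randomization, no place is given for the significant other's booklet, and the SCID interviews are stated to be blinded.
- **The 0.3 SD or the h = 0.22 as a yardstick for the bias.** Neither serves. The first is an assumption of the cited paper on pilot sample size; the second is a difference in remission proportions between CBT and psychodynamic therapy.

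**Conclusion.** The point holds as a risk built into the design, not as a demonstrated bias. As written, the protocol collects the T1–T7 patient self-reports, among them all three primary outcomes, at the treatment site of one arm, from patients who know their allocation. A setting effect that differs by arm would bias the endpoint comparison. If it also changes during therapy, it would bias the change contrast, and neither could be separated from treatment.

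The conclusion assumes that the sentence refers to the IMP premises. Direction and size are not established: the movement from 126 to between 198 and 350, or down to between 88 and 66, depends wholly on the assumed 0.1 to 0.2 SD and the assumed true 0.5 SD. The change is worth making because it is cheap and removes the asymmetry at source.

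**What to change.** In Therapy (T1 to T5) and in Follow-up (T6 and T7), replace the sentence on the place of assessment. Patients in both arms should complete the existing UNIPARK survey under identical conditions, through a personal link and away from either treatment centre, within the time windows already stated. Reminders should come from staff who deliver neither therapy.

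If the present sentence means only that the IMP administers the survey, say so in both places and state where patients complete it.

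The first patient was included in November 2014, so some assessments will already have been made. Where these took place on IMP premises, name this under Biases and limitations. Record the place of completion for each assessment, since a patient whose T1 was taken at the IMP would otherwise change setting unnoticed.

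The cost is small because the instrument is already online. The price is less supervision of completion, which reminders within the existing windows can largely offset.

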##### Follow-up (T6 and T7)

We will assess patients at 9 and 12 months after the beginning of therapy. Again, patients will participate in the online survey including the outcomes (Table 1). The assessment will be conducted at the IMP. The study will close 12 months after the beginning of therapy of the last included patient.

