**Design:**

This article describes the rationale and protocol of a prospective, open, interventive, balanced, bi-centric, pilot randomized controlled trial (RCT). A total of 32 patients with a primary SCID diagnosis of social anxiety disorder will be randomized to either CBT or ST. Both treatments will be manualized.

The primary outcome will include social anxiety symptoms at the end of therapy. Therapy will be restricted to no more than 26 hours (primary endpoint). Secondary outcomes will include psychological, social systems and interpersonal functioning, symptom adjustment, and caregiver burden, in addition to change measures, therapist variables and treatment adherence. At the secondary endpoints, 9 and 12 months after the beginning of therapy, we will again assess all outcomes.

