### Study procedures

#### Screening and diagnostic process

Interested individuals will initially take part in a telephone screening assessment of the main socially anxious symptoms (SCID, social anxiety disorder). Persons meeting the inclusion criteria will then receive the LSAS-SR self-report measure and SCID screening questionnaires together with the study information, informed consent and declaration about the DVD record use by post. After signing and sending back these documents, the documentation will be checked and the LSAS-SR score will be calculated and analyzed. If all documents are signed and the interested person shows a LSAS-SR >30, then the individual will be invited to a SCID-I and -II face-to-face interview, including the assessment of the general level of functioning (Global Assessment of Functioning; GAF). These pre-SCID interviews will be rated by independent raters with respect to both primary and secondary diagnoses. After inclusion based on shared decision making by clinical experts in the bi-centric case conference, persons will be randomized. Subsequently, they will be informed whether they will be treated in the CBT or ST study arm. Individuals will then attend a social network interview. In this interview they will select a significant other (e.g. partner, family member, best friend) who will then be asked to fill in a questionnaire booklet assessing significant others' burden.

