### Participation and attrition, responses to crises and suicidality

We will measure participation and attrition by counting the number of interested persons who will 1) contact the recruiting office, 2) participate in the initial screening, 3) will be SCID-interviewed, 4) included into the pilot study, 5) drop out before the beginning of therapy, 6) start therapy, 7) drop out during therapy, 8) end therapy, 9) participate in the 9 months follow-up, and 10) participate in the 12 months follow-up. We will describe causes for withdrawing, and calculate the retention rate for both study conditions separately and together.

Patients will be instructed to contact the therapist and/or research team whenever experiencing adverse events. No constraints will exist regarding additional therapeutic consultations. Inclusion criteria will, however, not allow for use of additional counseling or therapeutic support during the study period.

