#### Intention-to-treat and per-protocol analyses

The main analyses of all outcomes will be conducted on the intention-to-treat sample, comparing both treatment groups with 32 participants originally allocated after randomization [93]. This calculation will be regardless of whether the patients are detected to violate inclusion criteria, whether they complete therapy or not, or whether they are withdrawn from the study sample due to protocol deviations (e.g. changed use of medication, concurrent psychotherapy during the study period [94]). This will be followed by per-protocol analysis for the primary outcome measures (LSAS, SIAS, SPS) with only patients who fulfill all inclusion criteria, complete the intervention and do not deviate from the protocol.

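### T5, T6 and T7 are all timed from therapy, so a randomized patient who never starts has no outcome date, although the intention-to-treat analysis promises all 32

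*Protocol article*

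**What the plan says.** All passages are in the protocol article.

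- **Order of events.** Under Screening and diagnostic process, inclusion is followed by randomization, and then: "Subsequently, they will be informed whether they will be treated in the CBT or ST study arm". Therapy comes later.
- **Baseline.** Under Therapy (T1 to T5): "Baseline data (T1) will be scheduled no more than 5 days before the first therapy session".
- **Primary endpoint.** Same section: "The primary endpoint (T5) will be defined by a joint patient-therapist decision to end therapy or by the end of 26 hours of therapy".
- **Follow-up.** Under Follow-up (T6 and T7): "We will assess patients at 9 and 12 months after the beginning of therapy". Study closure uses the same origin: "The study will close 12 months after the beginning of therapy of the last included patient". The abstract agrees: "At the secondary endpoints, 9 and 12 months after the beginning of therapy, we will again assess all outcomes".
- **Drop-out foreseen.** The section on participation and attrition counts, as a stage of its own, included patients who "drop out before the beginning of therapy". It gives no expected rate.
- **Analysis set.** The intention-to-treat section commits the main analyses of all outcomes to "comparing both treatment groups with 32 participants originally allocated after randomization", whether or not therapy is completed.
- **Missing data.** The only rule, under Statistical analyses, replaces missing items when fewer than 20 % of a scale's items are missing.

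**The concern.** The analysis section promises results on everyone randomized, but the schedule defines outcome dates only for people who enter therapy. A patient who declines after learning the arm has no therapy to end, no 26th hour, and no start from which to count 9 or 12 months. Followed literally, the schedule gives nobody a date on which to ask that patient for an outcome. That differs from loss to follow-up, where a due assessment is missed.

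Whether a patient starts can depend on the arm. The trial is open, the arm is disclosed before therapy, each treatment is given at a single centre, and the Blinding section describes both centres as well known for their orientation. If never-starters contribute nothing, the T5, T6 and T7 comparisons are made among starters, with an exclusion after randomization that may be related to arm. If never-starters improve less than starters, this favours the arm that more patients decline. The pilot's stated purpose is to estimate effect sizes for sizing a confirmatory trial, so the distortion would carry forward.

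**Working it through.** **1. Dates for a never-starter, from the text.**

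| Assessment | Timed from | Date for a never-starter |
|---|---|---|
| Screening | before randomization | yes |
| T1 | up to 5 days before first session | only if a first session was booked and T1 was done before it |
| T2 to T4 | 8th, 15th, 20th therapy hour | no |
| T5 | end of therapy or 26 hours | no |
| T6, T7 | 9 and 12 months from start of therapy | no |

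The item-level rule cannot fill a whole missing questionnaire. Contrasts B and C in the mixed-design ANOVA run from T5 to 9 and to 12 months, so a patient without T5 cannot contribute observed data to them even if T6 and T7 are collected.

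**2. The plan's own sample-size figures.** For 0.3 SD, 80 % power and two-sided 5 %, the standard two-mean formula gives 175 per arm, 350 in total. For the pilot, N = 4 × (z₀.₈₀ / 0.3)² = 31.48, rounded up to 32, and 32/350 = 9.1 %. Both figures reproduce and neither is in dispute.

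**3. Precision.** The one-sided 80 % half-width with m patients, evenly split, is z₀.₈₀ × √(4/m). It is 0.298 SD for m = 32, 0.302 for 31, 0.307 for 30 and 0.313 for 29. One patient without data takes it past 0.3 SD, but the loss is small. The issue is selection.

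**4. How many patients (assumed rates).** With pre-therapy drop-out probability p, independent and equal in both arms:

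| p | Expected never-starters, 32p | P(at least one), 1 − (1 − p)³² | P(arms differ by ≥ 2) | P(arms differ by ≥ 3) |
|---|---|---|---|---|
| 5 % | 1.6 | 0.81 | 0.20 | 0.04 |
| 10 % | 3.2 | 0.97 | 0.36 | 0.13 |
| 15 % | 4.8 | 0.99 | 0.45 | 0.21 |

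The last two columns come from two independent Binomial(16, p) counts.

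**5. How large a distortion.** Assume never-starters do not improve and starters in either arm improve by d SD. With k of 16 never starting, the mean improvement of all allocated patients is d(16 − k)/16, and that of starters is d. Omission therefore shifts the arm mean by kd/16. The between-arm distortion is d × |k₁ − k₂|/16.

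For d, take 0.86 to 0.97, the CBT values the Efficacy section cites for SIAS and SPS, read here as within-arm change.

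- Arms differ by two: 2/16 × 0.86 = 0.11 SD to 2/16 × 0.97 = 0.12 SD, which is 36 to 40 % of 0.3 SD.
- Arms differ by three: 0.16 to 0.18 SD (54 to 61 %), but with probability of only 0.04 to 0.21.
- Expected |k₁ − k₂| is 0.90, 1.30 and 1.57 for p = 5, 10 and 15 %. At the mid-range d = 0.915, the expected absolute distortion is 0.05, 0.07 and 0.09 SD.

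For comparison, the standard error of a between-arm difference with 16 per arm is √(2/16) = 0.35 SD.

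**The case against.** A reader might infer that never-starters are dropped from the secondary endpoints. The article does not say so. The follow-up section speaks of patients without limiting them to starters, and the intention-to-treat section nominally keeps all 32. The defect is a schedule that cannot deliver a stated analysis, not a stated exclusion.

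A reader might also infer that the follow-up clock is wrong for everyone, or that T6 and T7 are a special case. Neither follows. Timing follow-up from therapy fits T1 to T5, and the article says its measurement times are aligned with the cited trials so that results can be compared. The gap also reaches the primary endpoint. Nor does every never-starter lack T1, because someone can complete it and then not attend.

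The stakes are limited. All analyses are descriptive and exploratory. Drop-out before therapy is counted, reasons for withdrawal are described and retention is reported by arm, so a differential refusal would probably be noticed. The binomial calculation uses the same rate in both arms, so it shows chance imbalance and does not demonstrate arm-dependent refusal.

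It can be said, too, that a fallback date is operational detail for the full protocol and that handling of whole missing assessments belongs in the analysis plan. The second part is fair. The first does not dispose of the point: the article states the schedule explicitly, the same way in several places, beside an analysis commitment that this schedule cannot meet. An analysis plan can treat missing values but cannot create an invitation that was never due.

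**Conclusion.** The point holds as a conflict between schedule and analysis set. T5, T6 and T7 have no date for a randomized patient who never starts therapy, a case the article itself foresees, while the main analyses of all outcomes are committed to all 32 allocated. Unless this is repaired, those comparisons risk being comparisons of therapy starters.

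The size cannot be established from the article. The illustration of about 0.05 to 0.09 SD expected, and 0.11 to 0.12 SD for a two-patient imbalance, rests on assumed drop-out of 5 to 15 % equal in both arms, no improvement in never-starters and d of about 0.9 in starters. It would be larger if refusal really differed by arm and smaller if never-starters also improved. It is small beside a standard error of 0.35 SD, but it is avoidable, and it bears on an effect size meant for planning the next trial.

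**What to change.** 1. In Therapy (T1 to T5) and Follow-up (T6 and T7), state that every randomized patient is invited to the outcome surveys. For a patient who never starts therapy, T6 and T7 fall due 9 and 12 months after randomization, and T5 gets a fallback calendar date, also counted from randomization and fixed in advance by the study team.
2. Where T1 is missing, use the screening LSAS-SR, SIAS and SPS as baseline. Table 1 marks all three at screening, but the screening text names only the LSAS-SR, so confirm that SIAS and SPS are collected then.
3. In the intention-to-treat section, include these patients in the between-group comparisons at T5, T6 and T7, using a method that does not require all seven time points. A follow-up survey alone would not make them complete cases for the planned mixed-design ANOVA.

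The cost is a few sentences and a few extra invitations to an existing online survey. Dates for patients who start therapy and the sample size of 32 are unchanged. The drawbacks are a slightly different time origin for these few patients and some non-response among them. The article reports the trial as still recruiting, so the change was feasible at that stage.
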